### Sample size

A pilot survey (unpublished data) conducted by the Amsterdam University Medical Centre team across both EDs over a 60-day period (weekdays from November 2019 to February 2020) identified 279 patients with a suspected infection and MEWS of ≥3, of whom 30 (11%) were diagnosed with sepsis. Extrapolating these findings suggests that approximately 1674 ED visits annually will involve patients with a suspected infection and MEWS of ≥3, of whom approximately 180 will be diagnosed with sepsis. The survey also showed that the overall ED population with MEWS ≥2 is twice as large. Using this lower MEWS threshold increases the chances of identifying patients at risk of developing sepsis. With this strategy, we aim to enrol 3300 participants in total.

### Statistical analysis

Data will be summarised using means and SD, or medians and interquartile ranges, depending on distribution of the data. Comparisons between groups will use appropriate parametric or non-parametric tests, depending on data distribution. Missing data will be addressed using multiple imputation analysis, if missing at random. Linear mixed effect models will account for dependencies in repeated measures. Dimensionality reduction techniques, such as principal component analysis and partial least squares discriminant analysis, will be used to explore and differentiate immunologic profiles within large transcriptomic or proteomic datasets. Regression models will be used to investigate associations between biomarkers and relevant outcomes. P values of <0.05 will be considered significant.

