#### Measurement of immune profiles

The immune response analyses used include mass spectrometry, proteomics, transcriptomics, metabolomics, microbiomics and Raman spectroscopy.

Raman spectroscopy is a non-destructive analytical technique that uses inelastic scattering of light to provide information on chemical composition of samples.^25 26^ Raman spectroscopy will be applied to plasma samples. In this way, it may be able to recognise immunological profiles and identify individuals at high risk of developing sepsis. Host response biomarkers, including those related to coagulation, inflammation and endothelial activation, will be measured in EDTA plasma using Luminex technology. In addition, a proteomic assessment of a broad range of mediators will be conducted using Olink technology (Olink Proteomics, Uppsala, Sweden). Targeted proteomic analysis using Olink technology has been used to identify pathophysiologically relevant alterations in proteins among critically ill sepsis patients.^27^ Furthermore, single-cell proteomics analyses will be performed using mass cytometry, focusing on cell signalling in innate immunity. Gene transcription profiles will be assessed through both whole-blood and single-cell RNA sequencing in a targeted subgroup of patients, using PAXgene tubes and viably frozen PBMCs (Becton-Dickinson, Breda, Netherlands). Identifying transcriptomic endotypes in sepsis patients can provide valuable information about the prognosis of sepsis patients receiving critical care.^15^ A mass spectrometry-based metabolomics platform will be used to assess metabolic profiles in patient plasma. Liquid chromatography-mass spectrometry-based analysis offers opportunity to explore potential sepsis biomarkers.^28^ Microbiota sequencing will be performed. In short, a repeated bead-beating method was used for DNA extraction. 16S ribosomal RNA gene sequencing will be performed on an Illumina system (San Diego, CA, USA) and further preprocessing of sequence data as described.^29 30^

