A key strength of our study is that we include a broad spectrum of ED patients with a suspected infection, capturing a range of patients with mild infections to severe sepsis. This design allows for effective discrimination between patients who become critically ill and those who recover rapidly. Longitudinal samples further provide insight into transient physiological immune activation versus pathological dysregulation of the immune system. The integration of diverse analytical approaches, including multiomics and microbiome profiling, allows for a comprehensive view of biological processes beyond conventional biomarkers like C-reactive protein and procalcitonin, whose predictive values for sepsis outcomes are limited.^11 51^ Another important strength is our ability to include severely ill patients unable to provide consent (eg, due to delirium), through consent from their legal representatives, ensuring representation of this vulnerable group.

However, the BIOSEP study faces several possible challenges. While broad inclusion criteria capture a diverse patient population, they may also result in a low number of events, such as sepsis or death. Since suspected infections are also included, not all patients are expected to have confirmed infections. Acute care research also presents logistical hurdles, leading to missed potential inclusions outside regular working hours. Enrolling patients in the acute phase can be particularly challenging, as immediate clinical care takes precedence, and patients may struggle to consider participation under their conditions. Additionally, while multiomics approaches provide rich datasets, translating these findings into practical bedside biomarkers remains a challenge.

Given its design, BIOSEP is primarily intended as a hypothesis-generating study. The large-scale integration of multiple omics data will allow for the identification of novel biomarker signatures and immune profiles associated with clinical outcomes. While external validation is beyond the scope of this study, the inclusion of patients from three diverse hospital settings may allow for internal cross-validation or subgroup analyses, enhancing the robustness and generalisability of the findings. These results may inform future validation studies in independent cohorts and guide the development of targeted diagnostic or therapeutic strategies.

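### A flat P<0.05 threshold with no stated multiplicity control leaves the share of false biomarkers uncontrolled in feature-wise omics analyses

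*Protocol article*

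**What the plan says.** The Statistical analysis section plans two kinds of test that can be run feature by feature. For groups: "Comparisons between groups will use appropriate parametric or non-parametric tests, depending on data distribution". For outcomes: "Regression models will be used to investigate associations between biomarkers and relevant outcomes". It also plans linear mixed models for repeated measures, and dimension-reduction methods that "will be used to explore and differentiate immunologic profiles within large transcriptomic or proteomic datasets". It then closes with a single rule: "P values of <0.05 will be considered significant". No platform, outcome or type of analysis is exempted, and nothing in the article mentions adjusted P values, a false discovery rate, a test hierarchy or a single primary outcome.

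The breadth of measurement is set out under Measurement of immune profiles: "The immune response analyses used include mass spectrometry, proteomics, transcriptomics, metabolomics, microbiomics and Raman spectroscopy". Two items there are clearly high-dimensional. One is sequencing: "Gene transcription profiles will be assessed through both whole-blood and single-cell RNA sequencing in a targeted subgroup of patients". The other is proteomics: "a proteomic assessment of a broad range of mediators will be conducted using Olink technology". Study endpoints and Table 2 relate the host response to mortality at four time points, length of stay, readmission and sequelae, among others.

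The Discussion calls the study primarily hypothesis-generating, places external validation outside its scope, and mentions internal cross-validation as a possibility. It also says that the integrated omics data "will allow for the identification of novel biomarker signatures and immune profiles associated with clinical outcomes".

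**The concern.** A per-test threshold of 0.05 limits the chance of a false positive for one test of one null feature. It does not limit the proportion of false findings in the set of features declared significant. That proportion depends on how many features are truly associated and on the power to detect them, and in omics screening both can be low.

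The second objective in the Introduction is to identify biomarkers associated with sepsis risk. Where such a biomarker is sought by testing features one at a time, this threshold decides what is reported. The Discussion expects the results to inform later validation studies, so false leads would use up effort and samples there. Nothing that the article commits to within this study would filter them out first.

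**Working it through.** **The plan's own figures.** The article gives no expected number or share of false findings, so there is no such figure to reproduce. Its only design calculation, under Sample size, is a recruitment projection: 279 × 360/60 = 1674 visits and 30 × 360/60 = 180 sepsis cases a year. Twice 1674 is 3348, close to the stated 3300, although the article does not spell out that last step. None of this involves power or an error rate, so the 0.05 threshold is set and not derived.

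**Inputs.**
- Threshold α = 0.05, from Statistical analysis.
- Number of features m, share truly associated π, and power: not in the document. All are assumed below and shown over a range.

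**Step 1: expected false positives for one outcome if every feature is null.** The expected count is α × m.
- m = 100: 0.05 × 100 = 5
- m = 1000: 0.05 × 1000 = 50
- m = 3000: 0.05 × 3000 = 150
- m = 20000: 0.05 × 20000 = 1000

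Correlation between features changes the spread of these counts but not their expectation.

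**Step 2: share of declared features that are false.** The ratio of expected counts is

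α(1 − π) / [α(1 − π) + power × π].

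At 80% power:
- π = 1%: 0.0495 / (0.0495 + 0.008) = 0.861
- π = 5%: 0.0475 / (0.0475 + 0.040) = 0.543
- π = 10%: 0.045 / (0.045 + 0.080) = 0.360

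For example, with m = 3000, π = 5% and 80% power, the expected counts are 3000 × 0.05 × 0.80 = 120 true and 3000 × 0.95 × 0.05 = 142.5 false.

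**Step 3: sensitivity to the assumed power.**

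| Truly associated | Power 0.30 | Power 0.50 | Power 0.80 | Power 1.00 |
|---|---|---|---|---|
| 1% | 94% | 91% | 86% | 83% |
| 5% | 76% | 66% | 54% | 49% |
| 10% | 60% | 47% | 36% | 31% |
| 20% | 40% | 29% | 20% | 17% |

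**Step 4: when are most declared features false?** Setting the ratio to one half gives π = α / (α + power), ignoring nothing else in the formula. At 80% power this is 0.05 / 0.85 = 5.9%. At power 0.50 it is 0.05 / 0.55 = 9.1%, and at power 1.00 it is 0.05 / 1.05 = 4.8%.

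**Step 5: where the exposure is greatest.** Sequencing is confined to a subgroup of unstated size. If 11% of patients have sepsis (the pilot figure, observed at MEWS ≥3, whereas the cohort starts at MEWS ≥2), the power at P<0.05 for a difference of 0.2 SD is 0.95 with 3300 patients, 0.51 with an assumed 1000 and 0.19 with an assumed 300. The smaller the subgroup, the further left in the table the analysis falls.

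**The case against.** The strongest reply is that this is silence and not error. The sentence does not say that the P values are unadjusted, the full protocol is in a supplement that is not shown, and omics multiplicity procedures are often left to an analysis plan. Part of this stands: a correction may exist elsewhere. But the article does more than stay silent. It publishes a threshold directly after describing the omics datasets and biomarker regressions, and neither limits it nor points to a correction.

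A second reply is that the study is exploratory, that later cohorts will validate the findings, and that no treatment decision or sample size depends on the threshold. This lowers the severity. It does not tell a reader what share of reported features to expect to be false, and cross-validation is offered only as a possibility.

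A third reply is that the methods named for the large datasets do not use P-value thresholds. That is correct for principal component analysis and partial least squares discriminant analysis, and the point is confined to feature-wise tests and regressions.

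Three stronger readings might be inferred, and the document does not support them:
- **That false findings would dominate in any case.** This depends wholly on assumed inputs. At 10% true and 80% power they are a minority.
- **That the plan uses plain two-sample tests, so that hospital and assay-batch differences enter as false signals.** The section asks for appropriate tests, also plans regression and mixed models, and does not exclude covariates. No batch scheme is described.
- **That every platform is tested at two sampling times.** Table 1 has rectal swabs on day 0 only, and day 4 blood comes only from patients still in hospital.

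**Conclusion.** The point holds for feature-wise omics tests and regressions. As written, the rule gives no control over the proportion of false findings. At 80% power that proportion is 86%, 54% or 36% when 1%, 5% or 10% of features are truly associated, and it exceeds one half only when fewer than about 6% are. That the tests number in the thousands is an inference from RNA sequencing and broad proteomics; the article gives no count. The conclusion that the error rate is uncontrolled does not depend on these assumptions, but its size does. Because the study is exploratory, this is a needed correction to the reporting rule and not a flaw in the design.

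**What to change.** Replace the closing sentence of the Statistical analysis section with:

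> For feature-wise omics analyses, associations are declared at a Benjamini-Hochberg false discovery rate of 5% within each platform, across all features and the outcomes tested; unadjusted P<0.05 applies only to non-omics clinical comparisons and is reported as exploratory.

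Pooling the outcomes within a platform matters, because a correction made separately for each outcome would leave the multiplication across outcomes unaddressed. The outcomes in each pool should be named before the analysis. The 5% level is a choice: an exploratory study could justify a more lenient rate, provided it is fixed in advance and reported. If the full protocol or analysis plan already contains such a rule, the article should state it or point to it.

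The change needs no new data or samples, and with recruitment expected to run until 2028 there is time to fix it in advance. The cost is that fewer features will be declared significant, and some true but weak associations will be missed, most of all in small subgroups.

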### Data management

All clinical data and outcomes will be manually extracted from the electronic health record into the Castor electronic data capture (Castor EDC) system. The questionnaires will be administered either by phone or digitally through Castor EDC. All patient data will be stored in accordance with local regulations and with the patient’s consent. Patient data will be pseudonymised to protect patient privacy. The encryption key will be available only to coordinating researchers. The research file will be password-protected and stored for 15 years. Inclusion in the BIOmarkers to diagnose SEPsis (BIOSEP) biobank means sample storage for up to 15 years. The study team will be responsible for data management. Local independent monitors will perform data validation checks and ensure that all study procedures comply with local regulations and protocol.

### Safety, adverse events and monitoring

The study will be monitored by the local clinical monitoring centre. According to the applicable Nederlandse Federatie van Universitair Medische Centra guidelines,^44^ the risk and burden to patients in this study are negligible. Given the negligible burden and risks for patients in this observational study, we will only report adverse events (AEs) and serious adverse events (SAEs) related to blood sampling. However, we do not expect any AEs or SAEs resulting from blood sampling. The investigator will report all SAEs to the sponsor promptly after becoming aware of them. The sponsor will then report these to the accredited Medical Ethical Committee that approved the protocol. For SAEs resulting in death or those that are life-threatening, reporting will occur within 7 days of first knowledge, with an additional 8 days allowed to complete the initial report. All other SAEs will be reported within 15 days of the sponsor’s first knowledge of the events.

### Patient and public involvement

None.

## Ethics and dissemination

The study was approved by the Amsterdam University Medical Centre’s Ethics Committee (No. 2022.0279) and will adhere to the Declaration of Helsinki and the Medical Research Involving Human Subjects Act (WMO). Verbal and written informed consent will be obtained from all participants or their legal representatives. Included patients were able to withdraw from the study at any time. Research results will be published in peer-reviewed journals.

## Discussion

The BIOSEP study is a large-scale investigation aimed at identifying early biomarkers relevant for the initial biological responses to infection and sepsis in an ED setting using a multiomics approach. Sepsis is a complex heterogeneous syndrome, involving an overactive inflammatory response alongside immune suppression, coagulation disruptions and alterations in the microbiome, all contributing to a failure to restore homeostasis.^45^ This heterogeneity suggests the existence of distinct biological phenotypes, underscoring the need to define the mechanisms of immune dysfunction to identify predictive markers and advance precision therapy.

Research into sepsis mechanisms has largely relied on animal models and data from ICU patients with sepsis, as defined by Sepsis-3 criteria.^4^ These studies have provided valuable insights into the pathophysiology, identifying endotypes based on gene expression profiles and immune responses.^15 16 46^ However, these findings primarily reflect advanced stages of the disease, by which point the window for early treatment has often passed. Timely detection and intervention are crucial for improving patient outcomes, yet our understanding of the initial immune responses remains insufficient.

A number of studies have applied omics-based approaches in ED settings, with promising results. For example, the transcriptomic classifiers IMX-BVN-2 and IMX-SEV-2, based on a 29-gene host expression signature, were able to differentiate between bacterial, viral and non-infectious illness (area under the curve (AUC) 0.80–0.90) and predict in-hospital mortality (AUC 0.84) among ED patients.^47 48^ A targeted proteomic study in paediatric ED patients used a three-protein panel (TRAIL, IP-10 and C-reactive protein) to distinguish bacterial from viral infections with high accuracy (AUC 0.90–0.92).^49^ Metabolomic profiling of blood samples from adult ED patients with suspected sepsis identified a six-metabolite panel that distinguished bacteremic sepsis from other acute conditions (AUC 0.93, accuracy 88%).^50^ While these studies support the potential of host-response-based diagnostics, they each focus on a single biological layer and typically address pathogen classification or compare highly selected patient groups. To date, no study has applied an integrative omics approach in a heterogeneous ED population of patients with suspected infection to enable early sepsis recognition and biologically meaningful patient stratification. The BIOSEP study aims to address this gap by focusing on ED patients with infections, at risk of progressing to sepsis. By employing a multiomics approach, BIOSEP seeks to unravel the host response during the early stages of sepsis and to identify new predictive biomarkers and potential therapeutic targets. This approach could enhance prognostic enrichment by linking early host response immune profiles to patient outcomes.

A key strength of our study is that we include a broad spectrum of ED patients with a suspected infection, capturing a range of patients with mild infections to severe sepsis. This design allows for effective discrimination between patients who become critically ill and those who recover rapidly. Longitudinal samples further provide insight into transient physiological immune activation versus pathological dysregulation of the immune system. The integration of diverse analytical approaches, including multiomics and microbiome profiling, allows for a comprehensive view of biological processes beyond conventional biomarkers like C-reactive protein and procalcitonin, whose predictive values for sepsis outcomes are limited.^11 51^ Another important strength is our ability to include severely ill patients unable to provide consent (eg, due to delirium), through consent from their legal representatives, ensuring representation of this vulnerable group.

However, the BIOSEP study faces several possible challenges. While broad inclusion criteria capture a diverse patient population, they may also result in a low number of events, such as sepsis or death. Since suspected infections are also included, not all patients are expected to have confirmed infections. Acute care research also presents logistical hurdles, leading to missed potential inclusions outside regular working hours. Enrolling patients in the acute phase can be particularly challenging, as immediate clinical care takes precedence, and patients may struggle to consider participation under their conditions. Additionally, while multiomics approaches provide rich datasets, translating these findings into practical bedside biomarkers remains a challenge.

Given its design, BIOSEP is primarily intended as a hypothesis-generating study. The large-scale integration of multiple omics data will allow for the identification of novel biomarker signatures and immune profiles associated with clinical outcomes. While external validation is beyond the scope of this study, the inclusion of patients from three diverse hospital settings may allow for internal cross-validation or subgroup analyses, enhancing the robustness and generalisability of the findings. These results may inform future validation studies in independent cohorts and guide the development of targeted diagnostic or therapeutic strategies.

To conclude, this multicentre study and biobank will provide critical insights into the immune dysregulation that occurs along the infection-sepsis spectrum and may offer new avenues for early prediction, diagnosis and treatment strategies.
